## Abstract

**Background:**

The prevalence of cognitive impairment in elderly diabetic patients is increasing, highlighting the importance of exploring strategies to prevent and ameliorate cognitive impairment in this population. Previous studies have focused mostly on improving cognition in elderly diabetic patients through three methods: medication, cognitive training, and lifestyle intervention. However, few studies have investigated the role of indoor biophilic environments in improving cognition. Biophilic environments improve human health by integrating natural elements into indoor architectural settings and have demonstrated efficacy in reducing stress and improving cognition. Therefore, it is worth exploring the effects of indoor biophilic environments on cognition in elderly diabetic patients. This study aims to investigate the effects of indoor biophilic environments on cognition in elderly diabetic patients, and the potential mechanisms.

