Constructing a therapeutic environment that incorporates various biophilic design elements in a real indoor environment is a challenging task, as the optimal biophilic elements remain ambiguous. Virtual reality (VR) technology can simulate the real environment and integrate various sensory stimuli (Riva et al., 2020), rendering the exploration of optimal biophilic elements or their combinations more cost-effective. In recent years, an increasing number of studies have utilized VR technology to construct biophilic environments and demonstrated its beneficial effects on cognitive performance (Latini et al., 2024; Yin et al., 2019). Thus, we first use VR technology to create biophilic environments with various biophilic elements and conduct a short-term trial to screen for the most effective biophilic elements or combinations. However, VR environments also have some limitations. Virtual environments have a side effect of motion sickness which will cause a biased evaluation of healing effects (Kiryu and So, 2007) and VR cannot replicate tactile sensations (Yu et al., 2019), which may miss the healing effects of touching biophilic elements (Hassan and Zhang, 2024; Jenkins, 1986). Additionally, conventional VR technology cannot mimic the comprehensive healing effect of biophilic elements. For example, it cannot simulate the air purifying effect of potted plants (Pettit et al., 2018) and the emotional support of companion animals (Amiot and Bastian, 2015; Liu et al., 2024; Acquadro Maran et al., 2022). In addition, VR also cannot simulate the effect of reducing sedentary time and increasing physical activity caused by watering plants (Dogra et al., 2017). Therefore, referring to the healing effect of each biophilic element in the short-term trial, appropriate biophilic elements will be selected for long-term indoor environment intervention. The specific arrangement of biophilic elements in the real environment will be designed to closely replicate the layout in the VR environment, ensuring the effects of the biophilic elements.

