The mechanisms underlying the impact of biophilic environments on cognition are not yet clear. A study suggests that biophilic environments may reduce the occurrence of neuroinflammation by alleviating stress, thereby improving cognition (Valentine et al., 2024), which is crucial in mitigating cognitive impairment associated with the E4 variant of apolipoprotein E (*APOE4*). *APOE4* is a strong genetic risk factor for cognitive impairment (Montagne et al., 2020). Previous studies have examined gene–environment interactions between *APOE4* and other environmental risk factors on cognitive functions. These studies mainly explored the interactions between diet (van de Rest et al., 2016), residential greenness (Zhu et al., 2020), physical activity (Pa et al., 2022; Stringa et al., 2020), and socioeconomic position (Frank et al., 2021) with *APOE4*. Investigating the interaction between *APOE4* and indoor biophilic elements on cognitive function helps us determine if biophilic interventions have different effects on populations with diverse genetic backgrounds.

Through the integrated approach of short-term VR and long-term real-environment interventions, we aim to explore the effects of indoor biophilic environments on cognitive function in elderly patients with diabetes. We use the results from the short-term VR trial as a reference for the long-term real environment intervention trial. The biophilic elements or combinations with the largest effect size and *p* < 0.1 in the short-term VR trial will be used in real indoor environments to validate their long-term effects on cognition in elderly diabetes. The findings of this research will not only contribute to supporting the design of VR scenarios for assessing the restorative impact of biophilic residential environments but also help develop cognitively improving living environments for elderly diabetic patients.

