Both the intervention and control groups will receive health behavior guidance, while the intervention group will additionally receive an indoor biophilic environment intervention. Health behavior guidance includes personalized health behavior and dietary guidance based on the Guideline for the prevention and treatment of type 2 diabetes mellitus in China (2020 edition) (Zhu and Society, 2021). Health promotion and personalized guidance will be conducted at each follow-up visit by medical doctors or professionals. The biophilic elements that are most effective in enhancing cognition during the short-term VR intervention trial will be used as the biophilic interventions in the long-term real environment intervention trial. Participants in the intervention group will be told to take the biophilic elements (such as indoor plants) home and place them in a visible place.

Long-term interventions will be followed up at 12 and 24 months. At the 12-month follow-up, behavioral risk factors, chronic disease history, Lubben scale for social interaction, PSQI, and DSST will be collected and a general physical examination will be performed. At the 24-month follow-up, behavioral risk factors, chronic disease history, Lubben scale for social interaction, PSQI, GDS-15, cognitive function (DSST, MoCA) will be assessed, a general physical examination will be performed, and blood samples will be collected again.

Blood samples will be collected in ethylenediaminetetraacetic acid (EDTA) anticoagulated vacutainer tubes. After centrifugation, blood cells and plasma will be stored separately. Plasma samples will be used for biomarker detection at both baseline and the 24-month follow-up, including glycated hemoglobin (HbA1c) levels, fasting blood glucose (FBG), tau phosphorylated at threonine 181 (p-tau181), endogenous secretory receptor for advanced glycation end-products (esRAGE), and interleukin-6 (IL-6). Blood cells will be used for DNA extraction and *APOE* genotyping. Blank control and duplicate samples will be used for quality control during the experiment.

At baseline and follow-up visits, we will fill out registration forms to record the use of the biophilic intervention facilities in the living room, in order to replace damaged biophilic elements in time and to provide persistent biophilic indoor environment intervention.

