#### Long-term real environment intervention trial

2.8.2

Primary outcome: cognitive function assessed by the DSST and MoCA scales, as well as concentrations plasma of p-tau181, esRAGE and IL-6.Secondary outcome: the amount of physical activity, blood pressure, scores of GDS-15 and PSQI. Participants will be asked to report the number of days per week they engage in vigorous physical activity (VPA), moderate physical activity (MPA), and walking, along with the daily duration of these activities. The metabolic equivalents (METs) of each study subject will be assigned and calculated based on the above information (Deng et al., 2008), and the amount of physical activity is the sum of METs.

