#### Long-term real environment intervention trial

2.12.2

The modified intention-to-treat population (mITT) will be used for statistical analysis. Missing values will be imputed using multiple imputation. Firstly, two sample t-tests (for continuous and normally distributed variables) and chi-square test (for categorical variables) will be conducted to assess the baseline equivalence between the intervention and control groups. Two sample t-tests will be used to compare whether cognitive scores are statistically different between two groups. Multiple linear regression will be used to demonstrate whether the intervention is statistically associated with cognitive scores after adjusting for potential confounders. Repeated measures ANOVA will be used to compare cognitive scores across groups. The potential confounders will be corrected in the mixed-effect model to determine the association between intervention and cognitive scores. If the intervention has a direct effect on cognitive function, longitudinal causal mediation analysis will be further used to clarify the mediating factors through which the intervention may affect cognition.

To explore the interaction of *APOE4* and the biophilic environment on cognition, we will perform stratified analysis according to groups to clarify the main effects of *APOE4* on cognitive function. Then, mixed models will be used to adjust for potential covariates and to elucidate the main effect of *APOE4* on cognitive function in each group. Finally, the interaction term between the *APOE4* and the intervention group will be included in the mixed-effects model to identify the effect of the genetic-environmental interaction on cognitive function.

In our study, all statistical tests are two-tailed, with a significance level of *p* < 0.05.

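### The mediation analysis is conditional on a direct effect, the wrong quantity, and the biomarkers and GDS-15 have no post-randomisation value before the final outcome visit

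*Protocol article*

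**What the plan says.** The abstract of the protocol article gives mechanisms as part of the purpose: "This study aims to investigate the effects of indoor biophilic environments on cognition in elderly diabetic patients, and the potential mechanisms". The introduction offers a biological route, citing another study ("biophilic environments may reduce the occurrence of neuroinflammation by alleviating stress, thereby improving cognition"), and also a behavioural one ("VR also cannot simulate the effect of reducing sedentary time and increasing physical activity caused by watering plants").

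Section 2.12.2 lists t-tests, multiple regression, repeated-measures ANOVA and a mixed model for cognitive scores. It then sets the condition for mediation: "If the intervention has a direct effect on cognitive function, longitudinal causal mediation analysis will be further used to clarify the mediating factors". It names no mediators.

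The visit schedule is in section 2.5.2. For blood: "Plasma samples will be used for biomarker detection at both baseline and the 24-month follow-up". For the first follow-up visit: "At the 12-month follow-up, behavioral risk factors, chronic disease history, Lubben scale for social interaction, PSQI, and DSST will be collected". At the second follow-up visit PSQI, the Lubben scale, behavioural factors and GDS-15 are recorded, and "cognitive function (DSST, MoCA) will be assessed, a general physical examination will be performed, and blood samples will be collected again". Section 2.8.2 lists the three biomarkers among the primary outcomes, after DSST and MoCA: "as well as concentrations plasma of p-tau181, esRAGE and IL-6".

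**The concern.** There are two separate problems.

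**The condition.** A total effect divides into an indirect part, which passes through the mediator, and a direct part, which does not. Requiring a direct effect before looking for mediators reverses the logic: the more completely a mediator explains the effect, the less direct effect is left to satisfy the rule. The condition also cannot be checked in advance, because the direct effect is defined relative to a chosen mediator and comes out of the mediation model. The models listed before it name no mediator, so they estimate total effects.

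**The timing.** Randomisation protects the comparison of arms on the mediator and on the outcome. It does not settle which of mediator and outcome came first. A biomarker whose only post-randomisation value comes from the same visit as the final cognitive test cannot be placed before that test.

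At stake is the mechanistic conclusion. The analysis could be omitted where mediation is strongest. A same-visit association between biomarker and cognition could also be read as a causal pathway when the opposite direction fits as well.

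**Working it through.** The plan states no figure on this point, so there is none to reproduce. The check sets the condition against the definition of a direct effect, and the mediators against the visit schedule.

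**Step 1: the condition**

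In a linear model without interaction, total effect = *c′* + *a* × *b*. Here *a* is the effect of arm on mediator, *b* the effect of mediator on outcome given arm, and *c′* the direct effect. Complete mediation means *c′* = 0, so a two-sided 5% test of the direct effect is passed about 5% of the time, whatever the size of *a* × *b*.

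Illustration, with 99 per arm (the number per group before allowance for loss to follow-up, section 2.11.2), two-sided 5% tests and 4,000 simulated trials. The effect sizes are assumptions, not trial figures: *a* = *b* = 0.7 in residual SD units and *c′* = 0.

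- Total effect = 0 + 0.7 × 0.7 = 0.49.
- Outcome SD within arm = √(1 + 0.7²) = √1.49 = 1.22, so the standardised total effect is 0.49 / 1.22 = 0.40.

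| Quantity tested | Significant in |
|---|---|
| Direct effect (the condition read literally) | 5.6% of trials |
| Total effect (the condition probably intended) | 80.1% |
| Indirect effect (both paths significant) | 99.8% |

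Under these assumptions the literal condition omits the analysis in 100 − 5.6 = 94.4% of trials. A total-effect condition omits it in 100 − 80.1 = 19.9%, although the indirect effect is almost always detectable.

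**Step 2: the schedule (section 2.5.2)**

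| Variable | Baseline | 12 months | 24 months |
|---|---|---|---|
| MoCA | yes | not listed | yes |
| DSST | yes | yes | yes |
| p-tau181, esRAGE, IL-6 | yes | not listed | yes |
| GDS-15 | yes | not listed | yes |
| PSQI | yes | yes | yes |
| Lubben scale | yes | yes | yes |
| Behavioural risk factors (physical activity is among them at baseline) | yes | yes | yes |

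The biomarkers and GDS-15 have one post-randomisation value, taken at the visit that supplies MoCA and the final DSST. The 12-month DSST even precedes that value. The last three rows have a 12-month value that can be placed before 24-month DSST and MoCA, with a baseline value of both mediator and outcome for adjustment.

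**Step 3: what same-visit measurement can do**

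A second illustration assumes no mediation at all. The arm shifts cognition by 0.5 SD, and cognition drives the biomarker measured at the same visit with slope 0.7. The effect of arm on the biomarker is then 0.5 × 0.7 = 0.35, with within-arm SD √1.49 = 1.22. With 99 per arm and 4,000 trials, an analysis treating the biomarker as mediator finds both paths significant in 51.5% of trials. The simulation uses no baseline values. It shows the direction of the risk, not its size in this trial.

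**The case against.** The strongest reply on the condition is that it is loose wording. The sentence follows the models for the association between intervention and cognition, so it most naturally means that mediation is pursued if those models show an effect. A technical direct effect could not work as a precondition anyway. This reading is probably right, and it limits the practical weight of the 5.6%. It does not rescue the term, which has a fixed and different meaning in the method named in the same sentence. Whether mediation should depend on a significant total effect is debated; the 19.9% above shows a possible cost, not an error in the plan.

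The strongest reply on timing is that the article never calls the biomarkers or GDS-15 mediators. Section 2.8.2 makes the biomarkers primary outcomes and GDS-15 a secondary one, and the mediator list may properly sit in an analysis plan not shown. This stands. The timing point is therefore conditional on their use as mediators, which the neuroinflammation route in the introduction makes plausible.

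A reader might infer that the mechanism aim cannot be answered at all, or that the label longitudinal is wrong throughout. The documents do not support either. Sleep, social interaction and self-reported behaviour are collected at 12 months, and the introduction itself mentions a physical-activity route.

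Finally, section 2.1 gives the main objectives of the long-term trial as the effect on cognition and its modification by *APOE4*. Mediation is not among them, which limits the stakes.

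**Conclusion.** The point holds in two limited parts.

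- **Condition.** Direct effect is the wrong quantity. The figure of about 5% applies only if the rule is read literally and mediation is complete; it does not estimate how often this trial would omit the analysis.
- **Timing.** p-tau181, esRAGE, IL-6 and GDS-15 have no post-randomisation value before the 24-month visit. If they are used as mediators, their order relative to 24-month cognition cannot be established. This follows from the schedule and does not depend on the simulations, whose effect sizes are assumed.

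Ordered mediation remains possible through the 12-month variables, on the assumption that the behavioural factors collected then include physical activity, as they do at baseline. The primary comparison, sample size and randomisation are untouched. The wording should be corrected before any unblinded analysis, because it determines what may be claimed about mechanism.

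**What to change.** In section 2.12.2, and in the analysis plan:

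1. Remove the direct-effect condition and estimate indirect effects regardless of the significance of the direct effect. At minimum, replace direct with total.
2. For the longitudinal causal mediation analysis, use mediators measured at 12 months (physical activity and other behavioural factors, PSQI, Lubben scale) with 24-month DSST or MoCA as outcome, adjusted for the baseline mediator and, where available, the baseline outcome.
3. Label any mediation analysis of p-tau181, esRAGE, IL-6 or GDS-15 as concurrent and exploratory. The comparison of arms on these variables at 24 months stays as planned.

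The cost is wording only: no extra visits, samples or participants. The downside is a weaker mechanistic claim for the biomarkers.

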### Data management

2.13

Data collected from participants will remain confidential. To ensure participant confidentiality, all personal identifying information will be securely stored separately from the study data, and access will be restricted to authorized personnel only. All data will be scrutinized and double-entered by the researchers using EpiData 3.1 to ensure accuracy. After verification, the data will be imported into SAS 9.4 for cleaning and storage.

### Quality control

2.14

We developed investigation manuals and provided standardized training for all personnel involved in the project, including VR operators, data collectors, clinicians, and laboratory staffs. Sequentially numbered opaque sealed envelopes are used for allocation concealment, and epidemiological data collectors will be blinded to mitigate information bias. After the face-to-face questionnaire survey, quality control procedures, including preliminary variable range and logical error checks, are conducted at the investigation site. Make sure the age of the subjects is accurate by checking the date of birth on their ID cards. In order to ensure the accuracy of diabetes diagnosis, we will further check the medical records or medication records of the self-report diabetes.

#### Short-term VR intervention trial

2.14.1

To ensure that participants’ attention is maximally directed towards the biophilic elements during the VR experience, VR operators explain the VR environment to participants and guide them in observing the biophilic elements during the experience.

#### Long-term real environment intervention trial

2.14.2

Biophilic intervention elements will be mailed to subjects, and project staffs will call them to confirm that they have received the intervention items. Usage instructions for the biophilic elements will be dispatched via cell phone message. Monthly follow-up will be conducted to ensure the maintenance of biophilic elements. Dead plants, animals, or damaged indoor decorations will be replaced to sustain the biophilic intervention.

A total of 2 mL whole blood sample will be collected by nurses with EDTA anticoagulant tubes. The blood samples will be centrifuged at room temperature at 1,500 rpm for 10 min. The separated plasma and blood cells will be stored in clearly labeled cryovials, respectively. Plasma and blood cells samples will be preserved in an ultra-low temperature freezer at −80°C. Plasma samples will be used for the quantitative detection of serum biomarkers (p-tau181, esRAGE, IL-6). Blood cells will be used for DNA extraction. Blank and positive controls will be incorporated into the experimental design to monitor non-specific reactions and reagent contamination.

To ensure follow-up rates, the following measures will be implemented: first, fully explain the purpose and procedures of the study to subjects during the recruitment phase. Second, participants will be asked to provide at least two types of contact information, including a mobile phone number, a fixed-line phone number, or a WeChat account. If participants do not reply during weekdays, attempts will be made on weekends. Third, appropriate incentives will be provided to the participants, including subject compensation and free health consultations offered by neurologists from tertiary hospitals.

### Safety

2.15

The anticipated risk to participants in this study is lower than that of routine physical examinations. Participants will be instructed to remove the VR headset if they have any adverse effects or discomfort.

## Discussion

3

Diabetes has become an increasingly critical public health problem, with a rising prevalence and high rates of disability and mortality. Moreover, diabetes is a major risk factor for cognitive impairment (Cukierman-Yaffe et al., 2020). Approximately 26% of people over 60 with diabetes suffer from MCI, and 36.9% have dementia (Jia et al., 2020). Cognitive impairment not only diminishes quality of life but also hinders diabetes management (Ojo and Brooke, 2015). Consequently, it is necessary to explore effective interventions to curb the progression of cognitive impairment in the elderly diabetic population.

Current researches primarily focus on conventional glucose-lowering treatments (Cukierman-Yaffe et al., 2020; Li et al., 2021; Ryan et al., 2006), cognitive training (Silverman et al., 2023; Wong et al., 2020), dietary nutrition (Lotan et al., 2021), and physical exercise (Chen Y. N. et al., 2023). Each of the four methods mentioned above has positive effects on cognitive function in diabetic patients. A common problem with these approaches is that their effectiveness depends on patient adherence. Biophilic design, a method of natural intervention, solves the problem of patient compliance and compensates for the shortcomings of the above methods. An increasing number of studies investigate the effects of biophilic design in indoor environments on health conditions (Lei et al., 2021; Li et al., 2022; Yin et al., 2019). However, most of these studies have focused on incorporating green vegetation, with most biophilic interventions involving short-term exposure through VR environments. Few studies have explored long-term interventions in real environments. In our study, we will evaluate diverse indoor biophilic elements, including both biophilic decorations and ornamental fish. Our study aims to identify the most effective biophilic elements or combinations for improving cognitive function by VR technology in elderly diabetic patients, and then use optimal biophilic elements for long-term real indoor environmental interventions. The findings from this study will be utilized to design a healing living environment in this population to effectively protect cognitive function. Furthermore, these findings could be applied to the design of biophilic environments in hospitals, nursing homes, and even private homes, providing therapeutic spaces that promote cognitive health. This practical application of biophilic design could help guide clinicians, architects, and healthcare providers in creating spaces that optimize cognitive health outcomes.

This study has the following strengths. First, the VR scene is designed based on a standard one-bedroom house displayed on a real estate platform in the project’s implementation area. Experiencing scenes close to real life in VR environments can weaken the bias of sensory experience caused by the strangeness of the virtual environments, and make the effect estimation of biophilic intervention more realistic and reliable. Second, the VR scene, including diverse biophilic design elements and interactive operations such as watering plants, feeding fish, opening doors, and pulling curtains, which provide a fully immersive VR experience, increases the authenticity of the VR environments and can maximize the simulation of the effect of the real environment intervention. Third, VR devices may impact cognitive function regardless of the specific VR intervention scene. To address this problem, cognitive tests will be conducted after participants use VR devices to experience both cluttered and clean environments. This approach may enable us to effectively control for potential confounding factors caused by the VR devices. Fourth, our study has both a short-term VR intervention and a long-term real environment intervention, which perfectly addresses the limitations of VR compared to real environments. Finally, since *APOE4* is the strongest genetic predisposition factor for cognitive impairment, exploring its interactions with the biophilic environment could provide evidence for formulating personalized interventions.

This study also has several limitations. First, the study is conducted in a single center and focuses only on elderly diabetics, which limits the generalizability of the findings. Second, the VR scene contains many furnishings, which may cause participants to ignore specific intervention elements assigned to them. To avoid this issue, researchers in the VR group assist subjects in noticing the assigned elements through verbal guidance and cues. Third, the Mini-Mental State Examination (MMSE) (Tsoi et al., 2015) and MoCA (Nasreddine et al., 2005) are widely used scales that comprehensively assess cognitive function (Islam et al., 2023; Miura et al., 2024), however, they lack sensitivity to detect immediate cognitive changes. Therefore, we use the DSST and BDS scales to evaluate cognitive scores in the short-term VR intervention trial. The DSST primarily assesses working memory and processing speed, while the BDS focuses on memory capacity and attention. Although they are not as comprehensive as MMSE and MOCA, they are more sensitive to short-term cognitive changes and are widely used in cognitive assessments (Cukierman-Yaffe et al., 2020; Greendale et al., 2021; Tian et al., 2015).
